#### Statistical Analysis

Statistical analyses will be performed according to a predefined statistical analysis plan (Table 2).

**Table 2 table2:** Statistical analysis plan details.

Objectives	Main outcomes	Key explanatory variables	Statistical methods
Compare PAP^a^ adherence and the PAP therapy persistence rate between different levels of home support provider service	PAP adherence: (1) mean number of hours/day of PAP use and (2) adherent patients defined as those with mean PAP use ≥4 hours/day PAP persistence: (1) percentage of days with PAP use, (2) patients still in therapy, and (3) patients still in therapy and adherent	Fixed effect: Level of service (standard of care, personalized care plan, or high service level) Random effect: Country	Multilevel model adjusted for selected confounding factors
Identify service components that influence PAP adherence and persistence	PAP adherence: (1) mean number of hours/day of PAP use and (2) adherent patients defined as those with mean PAP use ≥4 hours/day PAP persistence: (1) percentage of days with PAP use, (2) patients still in therapy, and (3) patients still in therapy and adherent	Fixed effect: Frequency of interactions, content of support, personalization of support, and telemonitoring Random effect: Country	Multilevel model adjusted for selected confounding factors
Identify factors associated with PAP adherence and persistence	PAP adherence: (1) mean number of hours/day of PAP use and (2) adherent patients defined as those with mean PAP use ≥4 hours/day PAP persistence: (1) percentage of days with PAP use, (2) patients still in therapy, and (3) patients still in therapy and adherent	Fixed effect: Frequency of interactions, content of support, personalization of support, telemonitoring, sociodemographic characteristics, OSA^b^-related clinical characteristics, and characteristics of PAP therapy Random effect: Country	Multilevel model
Descriptive Analysis	Sociodemographic characteristics OSA-related clinical characteristics OSA and PAP literacy Experience with PAP therapy Experience with home support provider support Quality of life Home support provider PAP-related service	N/A^c^	Usual descriptive statistics: Analysis by country
Describe patterns of PAP use	Mean PAP use categories over time	N/A	Data visualization such as Sankey diagrams

^a^PAP: positive airway pressure.

^b^OSA: obstructive sleep apnea.

^c^N/A: not applicable.

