### Outcome Measures

Study outcomes, time points, and data sources are summarized in Table 1. An ePRO tool will be used to administer the patient questionnaire. The ePRO tool was designed to assess various aspects of a patient’s status, condition, and experience at 2 time points: the time of ePRO completion and the beginning of PAP therapy. This included sociodemographic characteristics (age, relationship status, employment, education level, and social support), health status (BMI, smoking status, alcohol intake, comorbidities, sleep duration, and use medications to aid sleep), OSA-related factors (when PAP therapy was started, apnea-hypopnea index before starting PAP, and OSA symptoms), PAP therapy experience and satisfaction (tolerability of PAP, attitude to PAP, device noise, and level of motivation to use PAP), patient experience and satisfaction with home support providers, quality of life (including current health status), and OSA-PAP literacy. The full ePRO questionnaire is provided in Multimedia Appendix 1.

Home support provider service will be assessed using 4 components: frequency of interactions between the home support provider and a patient; content of support (logistical, educational, supportive, or behavioral); personalization of support according to patient profile or needs; and telemonitoring (telemetry, data visualization, and alerts triggering home support provider interventions).

**Table 1 table1:** Study outcomes.

Category and outcome		Time points	Source

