**Home support provider PAP-related service**			
	Number and type of interactions (home visit, phone call, and digital interaction) Number of mask changes Implementation of telemonitoring	1, 4, 6, and 12 months after starting PAP therapy and annually thereafter	ALH ERP

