**PAP persistence**			
	Percentage of days with or without PAP use defined as the ratio between the number of days with PAP usage (starting from 1 minute of use) over the number of days in the follow-up period Patients without PAP discontinuation (still in therapy), with temporary discontinuation, or with permanent discontinuation Patients still in therapy and with mean PAP use ≥4 h/day	4, 6, and 12 months after starting PAP therapy and annually thereafter	Device data and ALH ERP

^a^OSA: obstructive sleep apnea.

^b^PAP: positive airway pressure.

^c^ALH: Air Liquide Healthcare.

^d^ERP: Enterprise Resource Planning.

^e^ePRO: electronic patient-reported outcome.

^f^GORD: gastro-esophageal reflux disease.

^g^COPD: chronic obstructive pulmonary disease.

^h^PRO: patient-reported outcome.

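### The service-component model regresses adherence and persistence on realised contacts recorded on the same time grid, so the estimates are open to reverse causation and time-related bias

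*Protocol article*

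**What the plan says.** All references are to the protocol article.

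- **Aim.** Table 2 words the second objective causally: "Identify service components that influence PAP adherence and persistence". The third objective uses the same service terms but claims association only.
- **Model.** The component row of Table 2 gives "Fixed effect: Frequency of interactions, content of support, personalization of support, and telemonitoring Random effect: Country", adjusted for selected confounders. Under Multilevel Models these are linear or logistic mixed models. No lag, landmark or time-varying exposure is stated.
- **Exposure.** Table 1 lists, from the provider's ERP system, "Number and type of interactions (home visit, phone call, and digital interaction") at "1, 4, 6, and 12 months after starting PAP therapy and annually thereafter".
- **Outcomes.** Adherence uses the identical grid. Persistence uses "4, 6, and 12 months after starting PAP therapy and annually thereafter", which is that grid without month 1. One persistence outcome is the ratio of "the number of days with PAP usage (starting from 1 minute of use) over the number of days in the follow-up period".
- **What drives contacts.** Outcome Measures describes telemonitoring as including "alerts triggering home support provider interventions" and says support is tailored to the patient's profile or needs. The Introduction adds that French provider fees rise with hours of use.
- **Adjustment and checks.** The list under Confounding Factors holds baseline patient characteristics, severity at diagnosis and prescriber specialty. Sensitivity analyses cover the pandemic lockdowns and the device recall. The e-value analysis addresses unmeasured confounders. Limitations mentions neither reverse causation nor time-related bias.

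**The concern.** Two mechanisms can create a contact-outcome relation when contacts do nothing.

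1. **Reverse causation.** If a patient who is doing badly is contacted because of it, more contacts go with lower use in the same period.
2. **Accrual.** A patient who stops at month 3 has three months in which to be contacted, and a patient who continues has twelve. More contacts then go with persistence, and also with a higher share of days used, because time on therapy feeds both sides.

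The two can pull in opposite directions, so even the sign of a component effect could be wrong. The Discussion says the study will identify the most effective components, and that the research should inform payers about services and tariffs. With about 100,000 patients expected, a bias of modest size would come with a very small p-value.

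**Working it through.** The article gives no component effect to reproduce. The check asks what the stated model returns when the true effect of contacts is zero. All rates, standard deviations and stopping hazards below are assumptions; only the sample size of 100,000 comes from the article.

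**Reverse causation by hand.** Assume use ~ N(5, 2.3) h/day. Every patient has the same number of scheduled contacts. Alert contacts come at 0.3/month when use is below 4 h and at 0.1/month otherwise, over 12 months.
- z = (4 - 5)/2.3 = -0.435, so p = P(use < 4) = 0.332 and φ(z) = 0.363.
- Difference in mean contacts: Δ = (0.3 - 0.1) × 12 = 2.4.
- Cov(use, contacts) = -σφ(z)Δ = -2.3 × 0.363 × 2.4 = -2.00.
- Var(contacts) = mean + p(1 - p)Δ² = (0.332 × 3.6 + 0.668 × 1.2) + 0.222 × 5.76 = 2.00 + 1.28 = 3.27.
- Slope = -2.00/3.27 = **-0.61 h/day per contact** (simulated with use truncated to 0-10 h: -0.60).

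This is an extreme case, because all variation in contacts is alert-driven or noise. If scheduled contacts vary uniformly from 0 to 4 (variance 2), the slope is -2.00/5.27 = **-0.38** (simulated -0.37).

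**Accrual by hand.** For Poisson contacts at a constant rate, comparing patients on therapy for 12 months with patients who stop at month t, the odds ratio per contact is 12/t whatever the rate. At t = 6 it is 2.0. Simulated with 4 contacts/year and stopping hazards of 0.15 and 0.25 per year, it is about **1.9**.

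**Both together.** 100,000 patients in 4 countries (entered as indicators) over 12 months. Scheduled contacts at 0.15/month (triple in month 1), plus triggered contacts in months with use below 4 h. Low users stop more often; about 75% are still on therapy at month 12. Contacts have no effect.

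| Extra contacts/month when use is low | h/day per contact, all patients | h/day per contact, on therapy at month 12 | OR still on therapy, per contact | OR still on therapy, per 0.1 contact/month on therapy |
|---|---|---|---|---|
| 0 | +0.11 | 0.00 | 1.71 | 0.85 |
| 0.1 | -0.10 | -0.22 | 1.52 | 0.82 |
| 0.3 | -0.29 | -0.39 | 1.28 | 0.81 |
| 0.6 | -0.31 | -0.37 | 1.12 | 0.83 |

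Standard errors of the all-patient slopes are 0.002 to 0.004, so each false slope would be highly significant.

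**Count versus rate.** With contacts per month on therapy, the persistence bias reverses (last column). With contacts spread evenly, no triggering and stopping unrelated to contacts, the rate is close to unbiased (odds ratio 0.99 to 1.02). With even spreading but triggering, it is biased again (0.86 to 0.92).

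**Landmark model on the same data.** Contacts in months 1-4 are related to outcomes in months 5-12, among patients still on therapy.

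| Extra contacts/month when use is low | h/day per contact, not adjusted for earlier use | h/day per contact, adjusted | OR still on therapy, adjusted |
|---|---|---|---|
| 0 | -0.02 | -0.004 | 1.00 |
| 0.1 | -0.20 | 0.001 | 1.00 |
| 0.3 | -0.43 | 0.004 | 1.01 |
| 0.6 | -0.52 | -0.001 | 0.99 |

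Lagging alone does not remove the bias. Lagging with adjustment for earlier use returns the null.

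**The case against.** The strongest reply is that the article does not settle how the model will be built.

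- **Which frequency.** Table 2 says frequency, and nothing ties it explicitly to the realised counts in Table 1. The Introduction mentions regulated home visits, so a contracted frequency is possible and would largely avoid both biases. This stands as uncertainty, but realised contacts are the only frequency measure the article lists.
- **Alert criterion.** The article says alerts trigger interventions but not on what. Leaks or residual events could be the criterion. Low use is an inference, made plausible by needs-based support and the French fee rule. This stands.
- **Window pairing.** A shared grid does not prove that exposure and outcome come from the same window. Lags may be set in the analysis plan, and the full confounder list is in an appendix not shown. This stands as a reason for caution. Even so, Table 2 fixes the terms and model type, and the published adjustment list is confined to factors fixed at or before the start of PAP or to general patient characteristics.
- **Size.** The rates are invented, and a slope near -0.6 needs identical scheduled contacts for everyone. This stands.
- **Remedy.** A landmark drops early stoppers, and adjusting for early use removes any benefit that works through it. This stands, and is counted as a cost under the fix.
- **Standing of the objective.** Components are among the other objectives, not the main one. This stands.

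**Conclusion.** The concern holds as a risk built into the stated model: the component estimates are open to reverse causation and time-related bias, and nothing in the published adjustment or sensitivity analyses addresses either. With no true effect, the assumed scenarios give about +0.1 to -0.4 h/day per contact, and odds ratios for persistence of about 1.1 to 1.9 per contact when counts are used. Only the rough size should be relied on.

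Three stronger readings are tempting and not supported:

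- A reader might infer that the estimates are certainly reverse-caused. The alert criterion, the window pairing and the use of raw counts are not stated.
- A reader might infer a fixed direction, with contacts looking harmful for use and protective for persistence. The sign changes with triggering strength and with count versus rate.
- A reader might extend the point to the main service-level comparison. That uses three care categories, and no section assigns them from contacts received.

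**What to change.** For the component objective:

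1. Measure the service components in a fixed early window, for example from PAP start to month 4, among patients still on therapy at its end.
2. Relate them to adherence and persistence after that window, adjusting for device use within it. The simulation triggered contacts on use alone. If alerts also fire on leaks or residual events, adjust for those too; Table 1 already lists them as device data.
3. Where records allow, separate scheduled contacts from alert- or patient-triggered ones and base component conclusions on the scheduled ones.
4. Do not rely on contacts per month on therapy alone, which is biased when contacts are front-loaded or triggered.
5. If this is not done, reword the objective so that component results are reported as associations.

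The cost is analysis wording plus variables derived from dated provider and device records. The price in interpretation is that results apply only to patients still on therapy at the landmark, exclude early discontinuation, and omit any service benefit acting through early use. An unadjusted description of the early window should therefore be shown alongside, labelled as descriptive.

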**Methods:**

This real-world, ambispective, cohort study—conducted in France, Belgium, Spain, and Portugal—will recruit adults with OSA who started PAP therapy between 2019 and 2023 and were followed by an Air Liquide Healthcare home support provider. Given the large number of eligible participants (around 150,000), the study will use a decentralized and digital approach. A patient video will present the study objectives and the participation process. A secure electronic solution will be used to manage patient information and consent, as well as to administer a web-based questionnaire. Retrospective data, collected during routine patient follow-up by home support providers, include the level of service and device data, notably PAP use. Prospective data collected using an electronic patient-reported outcome tool include health status, OSA-related factors, patient-reported outcomes including quality of life and symptoms, OSA and PAP literacy, patient-reported experience, and satisfaction with PAP therapy and service. Hierarchical models, adjusted for preidentified confounding factors, will be used to assess the net effect of home support provider services on PAP adherence and persistence while minimizing real-world study biases and considering the influence of country-level contextual factors. We hypothesize that higher levels of home support provider services will be positively associated with adherence and persistence to PAP therapy.

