**Experience and satisfaction with home support provider**			
	Measured using a 5-point Likert scale for Home support provider availability for logistical support Home support provider availability for educational support Satisfaction with home support provider Perceived value of home support provider	At the time of ePRO completion	ePRO tool

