#### Patient Datasets

Retrospective data will be available for all included patients (included population). Prospective data from the ePRO tool will be available for the subset of patients who complete the questionnaire (ePRO population).

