### Limitations

Selection bias cannot be entirely ruled out because participants were required to have a valid email address or smartphone number to be eligible for the study. This may lead to underrepresentation of certain subgroups of PAP users, such as older adults. Patients who answer the questionnaire might also differ from those who do not answer it. In addition, this study will only include individuals who use PAP supplied by a home support provider affiliated with ALH and it is possible that the level or content of additional services may differ slightly from other home support providers in the same country. To assess the potential impact of such biases, we will compare the characteristics of our study population with published data on OSA, focusing on age, sex, and disease severity.

Data from the ePRO tool may be subject to recall bias and inaccuracy because participants will complete the web-based questionnaire at variable periods of time since the start of PAP therapy (up to 5 years later for those who started PAP in 2019) and medical data will directly be provided by the patient. Confounding bias other than the key confounding factors considered is another limitation, particularly with respect to medical follow-up (data that will not be collected in this study).

Finally, the period over which this study was conducted included times before and during the COVID-19 pandemic (including lockdowns), and the worldwide recall of a PAP device made by Philips Respironics [36]. Sensitivity analyses will be performed to determine whether these factors had any influence on the overall study findings.

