### Conclusions

The AWAIR study has a unique design, leveraging an unprecedented number of eligible participants, decentralized technologies, and a real-world comparative methodology across multiple countries. This approach will highlight intercountry differences in terms of patient characteristics, PAP adherence and persistence, PROs, PREs, and satisfaction with home support provider services. By assessing the added value of home support provider services, the results will support best practices for patient management and decision-making by health authorities and payers.

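### Questionnaire outcomes are described in completers only, without using the PAP data held on included non-completers; satisfaction is overstated if stoppers both answer less often and are less satisfied

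*Protocol article*

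**What the plan says.** The third group of aims under Study Objectives is a description, country by country, of literacy, experience, satisfaction, symptoms and quality of life. Table 2 (Statistical Analysis) gives the method for its descriptive row as "Usual descriptive statistics: Analysis by country".

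Patient Datasets separates two populations. On routine data: "Retrospective data will be available for all included patients (included population". On questionnaire data: "Prospective data from the ePRO tool will be available for the subset of patients who complete the questionnaire (ePRO population".

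The Abstract says the routine data "include the level of service and device data, notably PAP use". Table 1 adds therapy status under PAP persistence: "Patients without PAP discontinuation (still in therapy), with temporary discontinuation, or with permanent discontinuation". By contrast, items such as "Satisfaction with home support provider Perceived value of home support provider" come only from the questionnaire.

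Limitations concedes: "Patients who answer the questionnaire might also differ from those who do not answer it". The check it then announces compares the study population with published OSA data on age, sex and disease severity. Conclusions nevertheless promises a cross-country reading: "This approach will highlight intercountry differences in terms of patient characteristics, PAP adherence and persistence, PROs, PREs, and satisfaction".

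Entry differs by country (Ethical Considerations). French patients are included unless they object; patients in Belgium, Portugal and Spain must consent.

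**The concern.** Patients started PAP between 2019 and 2023, and enrolment began in October 2024, so some will be asked about their therapy years after leaving it. It is plausible, though not stated, that they answer less often and are less satisfied. A plain summary of completers would then lean towards each country's persistent users.

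The sponsor holds the variable most likely to drive this selection for patients who were included but did not complete. They are probably mainly in France, where a patient who ignores the invitation is still included. The announced external check does not compare completers with non-completers and does not involve PAP use or therapy status, so it could neither reveal nor correct the problem.

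At stake is the reading of the satisfaction and experience figures, and of differences between countries in them. The adjusted models for adherence and persistence are a separate matter and are not part of this point.

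**Working it through.** The article gives no completion rate, share of stoppers or satisfaction level, so there is no stated figure to reproduce. Every input below is an assumption.

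**Formulas.** Let s be the share of included patients who have stopped, r_u and r_s the completion rates in users and stoppers, and p_u and p_s the proportions satisfied.

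- All included patients: (1 − s)·p_u + s·p_s
- Completers only: [(1 − s)·r_u·p_u + s·r_s·p_s] / [(1 − s)·r_u + s·r_s]
- Effective sample after weighting by 1/r, as a fraction of completers (Kish): 1 / {[(1 − s)·r_u + s·r_s] × [(1 − s)/r_u + s/r_s]}

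**Base case.** s = 0.30, p_u = 0.90, p_s = 0.60, r_u = 0.30. The value for all included patients is 0.7 × 0.9 + 0.3 × 0.6 = 0.81.

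| r_s | Completers only | Overstatement | Effective sample |
|---|---|---|---|
| 0.20 | (0.189 + 0.036)/0.270 = 83.3% | +2.3 points | 1/(0.270 × 3.833) = 0.97 |
| 0.10 | (0.189 + 0.018)/0.240 = 86.3% | +5.3 points | 1/(0.240 × 5.333) = 0.78 |
| 0.05 | (0.189 + 0.009)/0.225 = 88.0% | +7.0 points | 1/(0.225 × 8.333) = 0.53 |

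**Smaller satisfaction gap.** With p_s = 0.75 the value for all included patients is 0.63 + 0.225 = 85.5%. Completers only read 86.7%, 88.1% and 89.0%, an overstatement of 1.2, 2.6 and 3.5 points.

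**Null cases.** If r_s = r_u, or if p_s = p_u, the two formulas coincide and the overstatement is zero.

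**Sensitivity to the inputs.** A separate set (p_u = 0.85, p_s = 0.65 or 0.45, s from 0.10 to 0.40, r_u = 0.30, r_s = 0.15 or 0.06) gives +0.9 to +11.3 points. The result is driven by what is assumed.

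**Between countries.** Take two countries with identical inputs (s = 0.30, p_u = 0.85, p_s = 0.45, r_u = 0.30; 73.0% satisfied in both), except that r_s is 0.15 in one and 0.06 in the other.

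- First: (0.1785 + 0.02025)/0.255 = 77.9%
- Second: (0.1785 + 0.0081)/0.228 = 81.8%

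The spurious gap is 3.9 points. With an assumed 5,000 completers the 95% half-width is 1.96 × √(0.78 × 0.22/5,000) = 1.1 points, so a large sample would make such a gap look firm.

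**What weighting recovers.** If completion depends only on therapy status, weighting by 1/r returns the figure for all included patients (81% in the base case). It says nothing about people who were never included.

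**The case against.** The strongest reply is that this is a condensed article. One table cell naming usual statistics does not rule out weights or a comparison of completers with non-completers in the full analysis plan. The questionnaire population is defined separately, and the limitation is disclosed. A description labelled as one of completers is not false. All of that is fair and keeps the point modest. It does not remove it: Table 2 is presented as the details of the analysis plan and names a method for this row, and the one selection check that Limitations announces is directed elsewhere.

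Three stronger readings are tempting, and the article does not support them.

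- A reader might infer that lower response among stoppers is enough to inflate satisfaction. Stoppers must also be less satisfied, which the article nowhere states.
- A reader might infer that hours of use are complete for every included non-completer. Patient Datasets does promise routine data for all included patients. However, Data Sources, Flow, and Management says device data arrive remotely or by memory-card download and must be reviewed for completeness, and the Introduction describes limited telemonitoring in some countries.
- A reader might infer that weighting would make the four countries comparable. In the opt-in countries, patients who do not consent are not included, so they cannot enter a response model.

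It is also fair that the statements about informing payers and authorities concern the value of services generally and are not tied to the satisfaction figures.

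**Conclusion.** The point holds as a conditional one. The plan describes questionnaire outcomes in completers by plain statistics, leaves unused the PAP data held on included non-completers, and relies on an external check that cannot see selection on persistence. Satisfaction is overstated if stoppers both answer less often and are less satisfied. Under the base-case inputs and the smaller satisfaction gap, the overstatement is about 1 to 7 points. It is zero if either condition fails, and no figure in the article fixes it. The direction of any effect on literacy or quality of life is not established here. This is an inexpensive improvement to a secondary descriptive aim and does not touch the main comparison.

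**What to change.** In the descriptive row of Table 2 and in Patient Datasets:

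1. Report questionnaire completion rates by country.
2. Compare completers with included non-completers, by country, on age, sex, start year, PAP use and therapy status, and show how complete the device data are.
3. Where included non-completers exist, present estimates weighted by the inverse probability of completion beside the unweighted ones, with that probability modelled on the same variables.
4. State that weighting does not correct non-consent in Belgium, Spain and Portugal. Weighted French figures would then refer to all non-objectors and figures elsewhere to consenters. Word intercountry statements on these outcomes accordingly.

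I would not standardise the four countries to one common distribution of PAP use, discontinuation and service level. Countries are expected to differ in exactly these features, so equalising them would remove real differences, and overlap in service may be poor.

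The cost is one response model per country on data already held, plus some precision. Across the base-case response rates the effective sample is about 53% to 97% of completers. At an assumed 5,000 completers, the worst of these widens a 1.1-point half-width to about 1.6 (1.15/√0.53). Selection on unrecorded factors remains.
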